## Abstract

**Background:**

In 2014 approximately 21,200 patients were diagnosed with oesophageal and gastric cancer in England and Wales, of whom 37 % underwent planned curative treatments. Potentially curative surgical resection is associated with significant morbidity and mortality. For operable locally advanced disease, neoadjuvant chemotherapy (NAC) improves survival over surgery alone. However, NAC carries the risk of toxicity and is associated with a decrease in physical fitness, which may in turn influence subsequent clinical outcome. Lower levels of physical fitness are associated with worse outcome following major surgery in general and Upper Gastrointestinal Surgery (UGI) surgery in particular. Cardiopulmonary exercise testing (CPET) provides an objective assessment of physical fitness. The aim of this study is to test the hypothesis that NAC prior to upper gastrointestinal cancer surgery is associated with a decrease in physical fitness and that the magnitude of the change in physical fitness will predict mortality 1 year following surgery.

**Methods:**

This study is a multi-centre, prospective, blinded, observational cohort study of participants with oesophageal and gastric cancer scheduled for neoadjuvant cancer treatment (chemo- and chemoradiotherapy) and surgery. The primary endpoints are physical fitness (oxygen uptake at lactate threshold measured using CPET) and 1-year mortality following surgery; secondary endpoints include post-operative morbidity (Post-Operative Morbidity Survey (POMS)) 5 days after surgery and patient related quality of life (EQ-5D-5 L).

**Discussion:**

The principal benefits of this study, if the underlying hypothesis is correct, will be to facilitate better selection of treatments (e.g. NAC, Surgery) in patients with oesophageal or gastric cancer. It may also be possible to develop new treatments to reduce the effects of neoadjuvant cancer treatment on physical fitness. These results will contribute to the design of a large, multi-centre trial to determine whether an in-hospital exercise-training programme that increases physical fitness leads to improved overall survival.

**Trial registration:**

ClinicalTrials.gov NCT01325883 - 29^th^ March 2011.

## Background

Worldwide, oesophageal cancer is the eighth most common cancer and the sixth most common cause of cancer death, while gastric cancer is the fifth most common cancer and third most common cause of cancer-death. In England and Wales, approximately 21,200 patients were diagnosed with oesophageal or gastric cancer in 2014, of which 37 % underwent planned curative treatment [1, 2]. Although potentially curative, surgical resection is attempted in up to 80 % of those patients planned for curative treatments, however significant morbidity and mortality is reported. The reported 90-day mortality rates for oesophagectomy and gastrectomy are 4.4 % and 4.3 % respectively, with 1-year survival rates between 76.1 % and 78.0 % depending on the site of the primary tumour [1]. A large updated meta-analysis provides evidence that for operable OG disease neoadjuvant therapies improve survival over surgery alone [3]. In the UK the MAGIC trial has resulted in a practice change in favour of neoadjuvant chemotherapy (NAC) [4]. Treatment with neoadjuvant therapies carries the risk of toxicity and in clinical practice this may be associated with an increased risk of surgical morbidity [3]. Cardiopulmonary exercise testing (CPET) provides an objective assessment of physical fitness through evaluating cardio-respiratory function under the stress of exercise mimicking the stress of major surgery. Variables derived from CPET such as oxygen uptake at estimated lactate threshold ($$ \overset{.}{\mathrm{V}}{\mathrm{o}}_2 $$ at $$ {\widehat{\uptheta}}_{\mathrm{L}} $$) and at peak exercise ($$ \overset{.}{\mathrm{V}}{\mathrm{o}}_2 $$ peak) are associated with worse outcome following UGI surgery [5, 6].

In a preliminary study, we showed, in a small number of patients, that neoadjuvant chemotherapy (NAC) before upper gastrointestinal (UGI) cancer surgery significantly reduced physical fitness [7]. In this study, lower baseline fitness was associated with reduced 1-year-survival in patients completing NAC and surgery, but not in patients who did not complete NAC. We therefore speculated that in some patients the harms of NAC may outweigh the benefits and set out to test the hypothesis that neo-adjuvant chemotherapy (or chemoradiotherapy) was associated with reduced physical fitness ($$ \overset{.}{\mathrm{V}}{\mathrm{o}}_2 $$ at $$ {\widehat{\uptheta}}_{\mathrm{L}} $$ measured using CPET) and that this fall in $$ \overset{.}{\mathrm{V}}{\mathrm{o}}_2 $$ at $$ {\widehat{\uptheta}}_{\mathrm{L}} $$ would in turn be associated with increased harm (mortality at 1 year) following surgery.

In this manuscript, we describe the design of a prospective, observational, observer blinded cohort study investigating the effects of neoadjuvant cancer therapies (both chemo- and chemoradio-therapy – NAC/CRT) on exercise capacity and clinical outcome in patients undergoing surgery for UGI cancer.

### Aims

The aim of this study is to test the hypothesis that the decrease in physical fitness associated with NAC/CRT prior to UGI cancer resection may outweigh the benefits (duration of survival) achieved by NAC/CRT in some patients. Specifically, we will test the following hypotheses in this patient group:

Primary hypotheses:Neoadjuvant cancer treatment will result in a decrease in physical fitness ($$ \overset{.}{\mathrm{V}}{\mathrm{o}}_2 $$ at $$ {\widehat{\uptheta}}_{\mathrm{L}} $$), measured using CPET.The change in physical fitness ($$ \overset{.}{\mathrm{V}}{\mathrm{o}}_2 $$ at $$ {\widehat{\uptheta}}_{\mathrm{L}} $$) associated with neoadjuvant cancer treatment will be associated with mortality 1 year after surgery. This second hypothesis will be evaluated in two separate ways:A)The relative decrease in physical fitness ($$ \overset{.}{\mathrm{V}}{\mathrm{o}}_2 $$ at $$ {\widehat{\uptheta}}_{\mathrm{L}} $$) associated with neoadjuvant cancer treatment prior to UGI cancer resection will be associated with mortality at 1 year after surgery.Secondary hypotheses:B)Patients whose physical fitness ($$ \overset{.}{\mathrm{V}}{\mathrm{o}}_2 $$ at $$ {\widehat{\uptheta}}_{\mathrm{L}} $$) changes their risk stratification category (low risk $$ \overset{.}{\mathrm{V}}{\mathrm{o}}_2 $$ at $$ {\widehat{\uptheta}}_{\mathrm{L}} $$ >14 ml.kg.^-1^min^-1^, medium risk $$ \overset{.}{\mathrm{V}}{\mathrm{o}}_2 $$ at $$ {\widehat{\uptheta}}_{\mathrm{L}} $$ 11.0–14.0 ml.kg^-1^.min^-1^, high-risk $$ \overset{.}{\mathrm{V}}{\mathrm{o}}_2 $$ at $$ {\widehat{\uptheta}}_{\mathrm{L}} $$ 8.0–10.9 ml.kg^-1^.min^-1^, highest risk $$ \overset{.}{\mathrm{V}}{\mathrm{o}}_2 $$ at $$ {\widehat{\uptheta}}_{\mathrm{L}} $$ <8.0 ml.kg^-1^.min^-1^) following neoadjuvant cancer treatment would have an increased 1-year mortality following surgery when compared with those who do not increase risk stratification category.Pre-NAC variables (including CPET derived variables) can be modelled to predict post NAC $$ \overset{.}{\mathrm{V}}{\mathrm{o}}_2 $$ at $$ {\widehat{\uptheta}}_{\mathrm{L}} $$.Exploratory hypotheses:The relative decrease in physical fitness ($$ \overset{.}{\mathrm{V}}{\mathrm{o}}_2 $$ at $$ {\widehat{\uptheta}}_{\mathrm{L}} $$) associated with neoadjuvant cancer treatment prior to UGI cancer resection will be associated with i) increased post-operative morbidity, assessed using the Post-Operative Morbidity Survey (POMS), and ii) worse patient reported outcome assessed using EQ-5D quality of life questionnaire.The relative decrease in peak oxygen consumption ($$ \overset{.}{\mathrm{V}}{\mathrm{o}}_2 $$ peak) associated with neoadjuvant cancer treatment prior to UGI cancer resection will be associated with i) increased post-operative morbidity, assessed using POMS, ii) worse patient reported outcome, assessed using EQ-5D quality of life questionnaire and iii) decreased 1 year survival.Patients with a lower exercise capacity ($$ \overset{.}{\mathrm{V}}{\mathrm{o}}_2 $$ at $$ {\widehat{\uptheta}}_{\mathrm{L}} $$ and $$ \overset{.}{\mathrm{V}}{\mathrm{o}}_2 $$ peak) tolerate NAC prior to upper gastrointestinal cancer resection (in terms of patient reported outcome and compliance with NAC protocol) less well than patients with a higher exercise capacity.Patients who do not tolerate NAC prior to upper gastrointestinal cancer resection (in terms of PROMS and compliance with NAC protocol) have a worse postoperative outcome (1-year mortality, POMS, EQ-5D).Changes in CPET derived variables will explain mechanisms of NAC associated exercise limitation.CRT (CROSS style chemoradiotherapy) will result in a greater fall in $$ \overset{.}{\mathrm{V}}{\mathrm{o}}_2 $$ at $$ {\widehat{\uptheta}}_{\mathrm{L}} $$ and $$ \overset{.}{\mathrm{V}}{\mathrm{o}}_2 $$ peak between pre- and post- neoadjuvant cancer treatments than NAC (MAGIC type chemotherapy).

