### Secondary outcomes

#### Physical fitness ($$ \overset{.}{\mathrm{V}}{\mathrm{o}}_2 $$ peak) and preoperative risk categories derived from CPET

CPET derived $$ \overset{.}{\mathrm{V}}{\mathrm{o}}_2 $$ at $$ {\widehat{\uptheta}}_{\mathrm{L}} $$ will be to stratify patients into preoperative risk categories after neoadjuvant cancer treatment: low risk $$ \overset{.}{\mathrm{V}}{\mathrm{o}}_2 $$ at $$ {\widehat{\uptheta}}_{\mathrm{L}} $$ >14.1 ml.kg^-1^.min^-1^; medium risk $$ \overset{.}{\mathrm{V}}{\mathrm{o}}_2 $$ at $$ {\widehat{\uptheta}}_{\mathrm{L}} $$ 11.0–14.0 ml.kg^-1^.min^-1^; high-risk $$ \overset{.}{\mathrm{V}}{\mathrm{o}}_2 $$ at $$ {\widehat{\uptheta}}_{\mathrm{L}} $$ 8.1–10.9 ml.kg^-1^.min^-1^; highest risk $$ \overset{.}{\mathrm{V}}{\mathrm{o}}_2 $$ at $$ {\widehat{\uptheta}}_{\mathrm{L}} $$ <8.0 ml.kg^-1^.min^-1^. CPET derived $$ \overset{.}{\mathrm{V}}{\mathrm{o}}_2 $$ peak will be defined as the average $$ \overset{.}{\mathrm{V}}{\mathrm{o}}_2 $$ over the last 30 s of exercise.

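### Hypothesis 2B: two sets of risk cut-points, improvers who fit both groups, and a reference group that takes in every patient already at highest risk

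*Protocol article*

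**What the plan says.** **Groups.** In Aims, item B states that patients whose fitness "changes their risk stratification category" "following neoadjuvant cancer treatment would have an increased 1-year mortality following surgery when compared with those who do not increase risk stratification category".

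**Cut-points in Aims.** Low risk is ">14 ml.kg.^-1^min^-1^, medium risk" 11.0 to 14.0, and high risk is "8.0–10.9 ml.kg^-1^.min^-1^, highest risk" below 8.0.

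**Cut-points in Secondary outcomes** (the subsection on preoperative risk categories). Low risk is ">14.1 ml.kg^-1^.min^-1^; medium risk" 11.0 to 14.0, and high risk is "8.1–10.9 ml.kg^-1^.min^-1^; highest risk" below 8.0.

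**Analysis.** The Statistical analysis section compares 1-year survival between change-in-fitness groups by a chi-squared or Fisher test, or by a log-rank test. It then plans logistic or Cox regression with adjustment for confounders. It does not define the change groups. The only group labels tied to a test are those for 2A under Sample size calculation (no change versus deteriorate). No sample size is given for 2B.

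**The concern.** 2B is introduced as one of two ways to evaluate the second primary hypothesis, although it is listed among the secondary hypotheses. Its result depends entirely on who is placed in which group. The article fixes that placement itself, in three ways that do not work together:

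- The same category has two boundaries.
- The two comparison groups are not complements of each other.
- The reference group collects every patient whom the scheme already ranks worst.

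Two competent analysts could build different groups from this text, with the data in hand. The third feature also weakens the contrast whichever set of boundaries is used. The Background reports that, in the preliminary study, lower baseline fitness went with reduced 1-year survival in patients who completed chemotherapy and surgery. The patients who cannot worsen in category are therefore expected to have high mortality.

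**Working it through.** **Nearest stated figure.** For 2A the article gives 242 patients for 30% versus 15%. With equal groups, n per group = [1.960·√(2·0.225·0.775) + 0.842·√(0.30·0.70 + 0.15·0.85)]² / 0.15² = (1.157 + 0.489)² / 0.0225 ≈ 120.5. This rounds up to 121, or 242 in total. The figure reproduces, but it belongs to 2A and nothing below depends on it.

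**Cut-points.** Values from 5.0 to 19.9 were classified by both texts.

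| Value | Aims | Secondary outcomes |
|---|---|---|
| 8.0 | high risk | none |
| 14.1 | low risk | none |
| all others, one decimal | one category | same category |

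If more decimals are kept, Secondary outcomes leaves 8.0 to <8.1 and >14.0 to 14.1 unclassified. Both sections leave >10.9 to <11.0 unclassified.

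**Group membership.** Four categories before and after treatment give 16 transitions.

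- 6 worsening transitions: index group only.
- 4 stable transitions: comparator only.
- 6 improving transitions: both groups, because the category changes and does not increase.

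**Ceiling.** None of the 4 transitions that start in the highest-risk category is an increase. All of these patients meet the reference definition, however far their oxygen uptake falls.

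**Size of the ceiling effect (illustration).**

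- From the article: change SD 3.8, and a mean change of −1 taken from the 1.0 difference that hypothesis 1 is sized to detect (both in Sample size calculation).
- Assumed: baseline mean 12, 13 or 14 with SD 3; a log-odds of death of −0.2 per ml/kg/min of post-treatment value; overall mortality 22.5%. A change SD of 2 is an assumed alternative.
- Model: logit(p) = a − 0.2 × post-treatment value, with a set to give 22.5%. Values are rounded to one decimal, the Aims cut-points are used, and improvers are placed in the reference group only.

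| Baseline mean | Change SD | Difference, all patients (points) | Difference, without baseline highest-risk (points) | Share lost |
|---|---|---|---|---|
| 12 | 3.8 | 14.5 | 18.8 | 4.3/18.8 = 23% |
| 13 | 3.8 | 17.3 | 19.8 | 2.5/19.8 = 13% |
| 14 | 3.8 | 19.7 | 21.0 | 1.3/21.0 = 6% |
| 12 | 2 | 7.3 | 11.1 | 3.8/11.1 = 34% |
| 13 | 2 | 9.9 | 12.1 | 2.2/12.1 = 18% |
| 14 | 2 | 12.2 | 13.4 | 1.2/13.4 = 9% |

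The mechanism can be checked by hand at mean 12, SD 3.8. Baseline highest-risk patients are 14.7% of the reference group with 41.9% mortality, and the rest have 12.4%. So 0.147·41.9 + 0.853·12.4 = 16.7%, against 31.2% in those who worsen: 31.2 − 16.7 = 14.5 and 31.2 − 12.4 = 18.8.

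Across the settings, baseline highest-risk patients are 2 to 9% of all patients and improvers are 7 to 20%. If improvers are also counted in the index group, as the literal wording allows, the difference at mean 12, SD 2 falls to 24.6 − 19.9 = 4.7 points.

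**Why exclusion alone is not enough.** When death was made to depend on baseline fitness only, so that change has no effect, the contrast without baseline highest-risk patients still showed 1.2 to 3.7 points. Baseline category therefore has to be handled in the analysis as well.

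**The case against.** The strongest reply is that the wording is loose but the intention is clear. The comparator is stated in terms of increasing risk, the predicted result is higher mortality, and the whole rationale concerns a fall in fitness. Read that way the two groups are exact complements. This is probably what was meant, and it largely answers the overlap point. It leaves a wording fault, since no other section confirms the reading, and it does nothing for the ceiling.

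It can also be said that every ordered scale has a top category, so comparing patients who moved up with everyone else is a definable contrast. That is true. The question is whether that contrast answers the hypothesis when the reference group includes patients who could not have moved.

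Three stronger readings are tempting and are not supported:

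- **That 2B has no adjusted analysis.** The Statistical analysis section plans regression adjusted for confounders, and Sample size calculation mentions adjustment for baseline exercise for 2A. What is missing is a statement that baseline category is adjusted for in 2B. That the crude test applies to 2B is itself an inference.
- **That the result could reverse.** No setting in the table does so. A sign change, of at most 2.4 points, appeared only when change in fitness was given no effect on death.
- **That a third of the effect is lost.** That is the worst case, at an assumed change SD of 2. At the article's 3.8 the loss is 6 to 23%.

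**Conclusion.** The point holds as a fault in definition. The cut-point contradiction is certain from the text but small, about 1.3 to 1.5% of post-treatment values under the assumed distributions. The overlap is certain on a literal reading and is probably a slip of wording. The ceiling is certain from the category scheme. It biases an unadjusted comparison, if that test is applied to 2B, towards no effect. The loss is 1.3 to 4.3 percentage points of mortality difference at the article's change SD, and is greatest when baseline fitness is low. These sizes rest on a baseline distribution, a mortality slope and an overall mortality that are assumed here. They show direction and order of magnitude only. Hypothesis 2A uses the relative decrease and does not depend on these categories.

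**What to change.** 1. Reconcile Aims and Secondary outcomes to one set of adjoining intervals, written so that every value falls in exactly one category at whatever precision is recorded. Which cut-points are clinically right is for the investigators.
2. Define the index group as patients who move to a higher-risk category, and the comparator as those who stay in the same category or move to a lower-risk one.
3. For the main 2B comparison, exclude patients who are in the highest-risk category at baseline, and stratify by baseline category (Mantel-Haenszel or stratified log-rank) or adjust for it in the regression. Report the contrast in all patients as a sensitivity analysis.

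The cost is a few lines of text and one stratified analysis, with no new data. The downside is that a few patients leave the main 2B comparison (2 to 9% in the illustration). They remain in 2A and in the sensitivity analysis.

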
## Methods

### Design

This study is planned as a multi-centre, prospective, observational, blinded (for physiological and surgical outcome assessments) observational cohort study, funded by the National Institute for Health Research for Patient Benefit Programme (PB-PG-0609-18262), approved for all NHS sites by the Dyfed Powys Research Ethics Committee (11/WA/0072) and registered with clinicaltrials.gov (NCT01325883). The study is to be conducted in four United Kingdom based NHS hospitals including; University Hospital Southampton NHS Foundation Trust, University Hospital Aintree NHS Foundation Trust, Lancashire Teaching Hospital and South Tees Hospital NHS Foundation Trust (above ethics number covers all four NHS sites).

### Participants

All patients listed to undergo NAC/CRT followed by elective UGI cancer resection (oesophagectomy and gastrectomy) are eligible for inclusion. Exclusion criteria are: inability to give informed consent, under 16 years of age, non-resectable disease, inability to perform CPET or bicycle exercise due to known contra-indication, and patients who declined surgery or neoadjuvant cancer treatment, or who received non-standard neoadjuvant cancer treatment.

### Recruitment

Patients who are candidates for curative surgery will undergo CPET both before and after neoadjuvant cancer treatment. All potentially eligible patients will be identified at the UGI multi-disciplinary meeting and approached with written information about the trial at the oncology/surgical outpatient appointment. All patients will be contacted by telephone to provide additional information about the trial and to confirm their eligibility. If the patient chooses to participate in the study, the first research visit is organised and written informed consent will be obtained together with all baseline measurements.

### Measurements

All patients will undergo a CPET and a patient reported outcome measure (PROM) questionnaire before neoadjuvant cancer treatment and also following completion of neoadjuvant cancer treatment (approximately 4 weeks following completion of neoadjuvant cancer treatment and immediately before planned surgery). Other outcome measures to be assessed following surgery are summarised in Table 1.

**Table 1 Tab1:** Outcomes and assessment measures used in the study

Outcomes	Assessment measure	Pre-neoadjuvant cancer treatment	Post- neoadjuvant cancer treatment	Day 3 Post-surgery	Day 5 Post-surgery	Day 7 Post-surgery	Day 15 Post-surgery	Day 30 Post-Surgery	1-Year Post-Surgery
Primary endpoint									
Physical fitness	Cardiopulmonary exercise test (CPET)	X	X						
Secondary endpoint									
Physical fitness to assess risk stratification	Cardiopulmonary exercise test (CPET)	X	X						
Exploratory endpoint									
Post-operative morbidity	Post-Operative Morbidity Score (POMS)			X	X	X	X		
Patient Reported Outcome	EQ-5D	X	X					X	X
Survival									X

“X” denotes measurement obtained at that time point. CPET – Cardiopulmonary exercise test; POMS – Post-Operative morbidity Survey

### Chemotherapy vs. Chemoradiotherapy

Due to the advent of CRT treatment during the conduct of this study, an additional hypothesis (number 9 above) has been added to those proposed in the original study protocol to explore any differences in impact on physical fitness between neoadjuvant cancer treatments, namely NAC (MAGIC type chemotherapy) and CRT (CROSS style chemoradiotherapy).

### Primary outcome

#### Physical fitness ($$ \overset{.}{\mathrm{V}}{\mathrm{o}}_2 $$ at $$ {\widehat{\uptheta}}_{\mathrm{L}} $$) derived using CPET

CPET will be used to assess physical fitness pre- and post-neoadjuvant cancer treatment. Patient and surgical characteristics recorded at first CPET will include age, gender, height, weight, diagnosis, staging, planned procedure. Height and weight will also be recorded at the second CPET. All CPET’s are performed in-hospital by trained and experienced staff with full resuscitation capability. All efforts will be made to conduct the tests to facilitate other clinical appointments. Each individual CPET is conducted at a similar time of day. Participants will be asked to refrain from caffeine ingestion and strenuous exercise prior to the test for at least 2 h. All CPET’s will be performed using an electromagnetically braked cycle ergometer (Ergoline 2000), 12 lead ECG, non-invasive blood pressure, pulse oximetry and a metabolic cart (Geratherm Respiratory GmbH, Love Medical Ltd). Patients were asked to perform an incremental ramp test to the limit of tolerance and to maintain a cycling cadence at 55–65 revolutions per minute (rmp) throughout the test. CPET assesses the amount of oxygen extracted from the inspired gas in a given period of time, expressed as $$ \overset{.}{\mathrm{V}}{\mathrm{o}}_2 $$ at $$ {\widehat{\uptheta}}_{\mathrm{L}} $$ and $$ \overset{.}{\mathrm{V}}{\mathrm{o}}_2 $$ peak. Ventilatory equivalents for oxygen and carbon dioxide ($$ {\overset{.}{\mathrm{V}}}_{\mathrm{E}}/\overset{.}{\mathrm{V}}{\mathrm{o}}_2 $$ and $$ {\overset{.}{\mathrm{V}}}_{\mathrm{E}}/\overset{.}{\mathrm{V}}{\mathrm{co}}_2 $$) are measurements of the ventilatory requirement for a given metabolic rate. Estimation of $$ \overset{.}{\mathrm{V}}{\mathrm{o}}_2 $$ at $$ {\widehat{\uptheta}}_{\mathrm{L}} $$ will be performed using a conventional cluster of variables (breakpoint in the $$ \overset{.}{\mathrm{V}}{\mathrm{o}}_2 $$ and $$ \overset{.}{\mathrm{V}}{\mathrm{co}}_2 $$ relationship), with increases in $$ {\overset{.}{\mathrm{V}}}_{\mathrm{E}}/\overset{.}{\mathrm{V}}{\mathrm{o}}_2 $$ and end-tidal oxygen partial pressure but no increase in $$ {\overset{.}{\mathrm{V}}}_{\mathrm{E}}/\overset{.}{\mathrm{V}}{\mathrm{co}}_2 $$ or fall in end-tidal carbon dioxide partial pressure PETCO_2_ [8]. Evaluation will be undertaken independently by two experienced assessors, blinded to each other’s assessments, with disagreement resolved by a third assessor. The multi-disciplinary team caring for the patients will not be provided with any information regarding outcome measures.
